### Covariates

Factors previously shown to be associated with adherence will be assessed using surveys administered to the caregiver upon enrollment and at 30 and 60 days. We adapted a version of the Integrated Behavior Model [26] as a unifying conceptual framework to contextualize these factors that may be influencing adherence patterns. These include medication beliefs, social norms, self-efficacy, intention to adhere to controller medications, asthma knowledge and skills, environmental constraints (routines, responsibility, and conflict over medication taking), and demographics (see Figure 2).

The Beliefs About Medicines Questionnaire [27] will be used to assess medication beliefs (perceived necessity and concerns regarding ICS use). Descriptive and injunctive social norms will be assessed with separate questions. We will use question blocks from the Caretakers Expectation Scale [28] to assess perceived importance of asthma-related tasks and self-efficacy for each task. The caregiver will be asked to estimate both prior adherence in the previous four weeks, as well as adherence intention for the next 4 weeks. The Asthma Knowledge Questionnaire [29] will assess a basic caregiver understanding of asthma symptoms, triggers, and treatments. The Asthma Routines Questionnaire [30] will measure the strength of routines surrounding asthma care. The Asthma Responsibility Questionnaire [31,32] will assess the degree to which children and caregivers share responsibility for managing asthma. Parent-child conflict over medication use will be measured with 2 questions developed by the study team (see Multimedia Appendix 2).

Demographics will include the caregiver’s relationship to the child, age, marital status, family income level, education level, and whether or not he or she is the child’s primary caregiver. Child demographic information will include the child’s race, ethnicity, age, and number of nights per week he or she typically stays with the primary caregiver.

**Figure 2 figure2:**
[figure not shown]
Conceptual framework adapted from the Integrated Behavioral Model.

### Intervention

#### Enrollment

Potential subjects will be screened through the daily census listings for the ED and general pediatrics inpatient units at CHOP, using the protocol inclusion and exclusion criteria. Parents of eligible participants will be approached for informed consent, screening, and enrollment prior to the patient’s discharge from the hospital. Child assent will be obtained from children ages 7 years and older, unless the child is judged to be incapable of assent. If subjects provide consent and enroll, they will complete the initial study visit prior to hospital or ED discharge. As part of enrollment, caregivers will complete an initial 30-minute survey on the Way to Health (WTH) platform (see below for description). Prior to survey completion, participants will be randomized into either the control or intervention group using a 1:1 randomization scheme, stratified by location (ED or inpatient). Each participant will be compensated US $20 through a reusable debit card following completion of each survey, for a total of US $60 for those completing the entire study.

Following the baseline survey, a study team member will attach an electronic sensor to the participant’s ICS inhaler. If the participants do not have a currently filled ICS prescription with them in the hospital room, they will be instructed on how to attach the sensor to the child’s inhaler when they get home. Participants whose sensors are not attached to the inhaler at discharge will be contacted by phone to achieve an initial sync. Participants who have mobile phones will download the Propeller mobile phone app for data transmission purposes, but the participants will not have access to any information from the app. Preferences for the text messages, which are delivered to the parents’ mobile phone via the Way to Health platform (time of day and preferred phone number), will be collected for all participants. Participants will be instructed to use the inhaler as directed by their physician and that they may begin to receive automated text message reminders regarding their child’s medication use.

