#### Limited Efficacy

Limited efficacy outcomes for this study will include (1) percent ICS adherence, as measured by electronic monitoring and (2) average change in parent-reported asthma control, assessed using the parent-reported portion of the child Asthma Control Test [25]. Inhaled controller medication use will be measured in both groups using electronic sensors (see description below) affixed atop of the MDI canister. ICS adherence will be calculated from the daily medication use data as the average percent adherence (observed actuations or prescribed actuations) for the intervention group versus the control group for the 30-day intervention phase. The average change in the parent-reported portion of the child Asthma Control Test score between enrollment and the 30-day follow-up call will be calculated for the intervention and control groups.

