### Data Analysis

#### Feasibility

Response rate will be defined as number of participants who complete enrollment, out of the total number of eligible patients who we approach. Passive retention will be evaluated using the median number of days for which the sensor syncs with its mobile phone or hub. Qualitative reasons for missing actuation data (eg, logging out of the app, failing to plug in the hub, or prescription changes) will be recorded if described by the caregiver during follow up or syncing issue calls described above. We will use summary statistics (mean, interquartile range) to describe Likert-based usability, acceptability, and preferences question responses. Qualitative responses regarding what participants liked most about the study and what would make it better will be evaluated for the most common responses.

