#### Limited Efficacy

Bivariate testing will be conducted to assess whether the intervention and control groups are balanced on key characteristics, including demographics, baseline asthma control (based on Child Asthma Control Test score on enrollment), and baseline medication adherence. If the groups are balanced, differences in 30-day adherence proportions and parental perceptions of asthma control between the intervention and control groups will be assessed using *t* tests or Wilcoxon Mann-Whitney tests depending on the distribution of the data. If the groups are unbalanced, regression models will be used to adjust for the unbalanced measured confounders.

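### Randomisation comes before the baseline survey is completed, so the survey-based baselines are not secured as pre-randomisation measures

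*Protocol article*

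**What the plan says.** The Enrollment section puts the survey inside enrolment ("As part of enrollment, caregivers will complete an initial 30-minute survey on the Way to Health (WTH) platform") and then fixes the order: "Prior to survey completion, participants will be randomized into either the control or intervention group using a 1:1 randomization scheme". Sensor attachment is described as following the survey.

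The content of that survey matters to the analysis in four places.

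- Covariates: at enrolment and at later calls, caregivers are surveyed on factors linked to adherence. They are asked to "estimate both prior adherence in the previous four weeks, as well as adherence intention for the next 4 weeks".
- Outcome Measures, Limited Efficacy: the change in parent-reported asthma control "between enrollment and the 30-day follow-up call will be calculated for the intervention and control groups".
- Data Analysis, Limited Efficacy: the balance tests cover demographics, "baseline asthma control (based on Child Asthma Control Test score on enrollment), and baseline medication adherence". Their result selects the analysis: "If the groups are unbalanced, regression models will be used to adjust for the unbalanced measured confounders".
- Data Analysis, Feasibility: "Response rate will be defined as number of participants who complete enrollment", divided by the eligible patients approached.

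On what families know about their arm, the Enrollment section says that message preferences are taken from every participant and that everyone is told that "they may begin to receive automated text message reminders". The Way to Health Platform section says that the platform automates randomisation and also stores the survey data. The Intervention Phase section starts the randomised intervention on the day of discharge.

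**The concern.** A baseline used for a change score, a balance check or an adjustment should be out of reach of the allocation. The usual safeguard is to complete it before the arm is generated. Here the stated order is the reverse, and the items at issue are subjective caregiver reports. Intention to adhere over the coming four weeks is an obvious example: a caregiver who knows that daily reminders are coming may answer differently from one who knows that they are not.

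Two things are at stake. First, if the arm were known during the survey, a difference in reporting would enter the change in asthma control, the balance tests, the choice between unadjusted test and regression, and any covariate adjustment. Second, a family that stops partway is already randomised. It lacks a complete baseline and, since the survey belongs to enrolment, it would not count towards the response rate.

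**Working it through.** The article gives no figure for this point, so there is nothing of its own to reproduce. The check is of sequence first and then of size.

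**Sequence.**

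1. The survey is part of enrolment, and assignment precedes its completion (Enrollment). This is a stated order, not a detail left out.
2. Prior adherence and intention are collected in the enrolment survey (Covariates), so both may be recorded after assignment.
3. The asthma control score is taken on enrolment (both Limited Efficacy sections). That it sits in this survey is an inference, because the Enrollment section does not list the survey's content.
4. The wording could mean before the survey starts or partway through it. Some items may therefore precede assignment, but the text secures this for none of them.
5. Nothing described needs the arm earlier. The sensor step follows the survey, and the reminders start at discharge.

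**Size of a loss.** Inputs: 40 children (Participants), 1:1 (Enrollment).

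- Per arm: 40 / 2 = 20. One randomised non-finisher: 1/20 = 5% of an arm.
- The article gives no non-completion rate, so 5%, 10% and 15% are assumed here: 40 × 0.05 = 2, 40 × 0.10 = 4 and 40 × 0.15 = 6 families without a complete baseline.
- Difference detectable at 80% power, two-sided 5%, for analyses that need a baseline: (1.960 + 0.842) × √(2/n), in SD units. These error rates are also assumptions, as the article claims no power.

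| Non-completion (assumed) | n per arm | Detectable difference |
|---|---|---|
| 0% | 20 | 0.89 SD |
| 5% | 19 | 0.91 SD |
| 10% | 18 | 0.93 SD |
| 15% | 17 | 0.96 SD |

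The loss of precision is small.

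**Size of a reporting shift, if the arm were known.** Change = follow-up − baseline, so a shift b in one arm's baseline report moves that arm's mean change by −b. With b in SD of the change score and SE = √(2/20) = 0.316, the type I error of a nominal 5% test is Φ(−1.96 + b/SE) + Φ(−1.96 − b/SE) (normal approximation).

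| Shift b (assumed) | b/SE | Type I error |
|---|---|---|
| 0 (no disclosure) | 0 | 5% |
| 0.1 SD | 0.32 | 6% |
| 0.2 SD | 0.63 | 10% |
| 0.3 SD | 0.95 | 16% |
| 0.5 SD | 1.58 | 35% |

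The shifts are illustrative. Nothing in the article supports any particular non-zero value.

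**The case against.** The strongest reply is that the order alone does no harm. A baseline recorded after assignment, but before treatment and without knowledge of the arm, has the same expectation in both arms and remains usable for change scores and adjustment. Several features suggest that families did not know: randomisation is automated, preferences are taken from controls too, everyone hears the same conditional statement about reminders, and daily reminders begin only at discharge. Conditional wording would make little sense to families already told their arm. This stands. A reader might infer from the order that the baselines are biased or unusable; the article does not support that. What remains is that these features make disclosure less likely without excluding it. The only blinding described (Propeller Health System) concerns staff and medication-use data, not the arm.

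A reader might also infer that families who do not finish the survey are dropped from analysis. The article does not say so. Its phrase about completing enrolment defines the numerator of a response rate, not an analysis set, and rules for incomplete baselines may well be in the full protocol or analysis plan. Further, the survey is one sitting before discharge, paid on completion, and sensor-measured adherence needs no survey data unless adjustment is triggered.

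Finally, the primary outcomes concern feasibility, and the Limitations section says that the study is not powered for between-group differences in adherence. That limits the weight of the point but does not remove it, because the same section intends the differences to inform later efficacy testing.

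**Conclusion.** The point holds in a limited form. The stated order leaves prior adherence, intention and, by inference, the asthma control score unsecured as pre-randomisation measures, and it allows families to be randomised without a complete baseline. Whether any bias follows depends on whether the caregiver or the staff present knew the arm during the survey, which the article does not settle. With no disclosure the error rate stays at its nominal level; the inflated values hold only under the assumed shifts. The cost of incomplete surveys in precision is slight at any of the assumed rates. In an unpowered feasibility pilot this is of minor to moderate weight, and it is worth correcting mainly because the correction costs almost nothing.

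**What to change.** For remaining enrolment, set the platform to randomise on submission of the baseline survey, and in any case before discharge. If the trigger cannot be moved, withhold the arm from caregiver and staff until submission, and say so. The first option removes both the disclosure risk and randomised families without a submitted baseline; the second removes only the disclosure risk.

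For families already enrolled (enrolment began in December 2015), report whether the arm was hidden until submission and how many were randomised without a complete survey. Keep every randomised family in the sensor-measured adherence comparison. Repeating the change-score analysis with and without the earlier enrollees would add little with 40 children.

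The cost is one platform setting, a one-line amendment and two sentences in the report. One system already handles both randomisation and surveys, so no extra visit or staff should be needed.

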#### Intervention Phase

The randomized intervention begins the day of discharge from the hospital and lasts 30 days. During this time, the intervention group will receive daily automated text message reminders from the WTH platform at a time of their choosing. In addition to daily text message reminders for the intervention group, both the intervention and control groups will receive programmed text messages when they reach milestones in the study, such as survey or intervention completion. These text messages will also serve as prompts to contact study staff and complete their next survey. The research team will also program text messages reminding participants to continue syncing their electronic monitoring sensor with its receiver by turning on their Bluetooth, if they are using a mobile phone, or by making sure that their hub is plugged in, if not. A total of 3 syncing reminders will be sent over the course of the intervention. Study staff will send individualized text messages or call participants if the sensor fails to sync in the first 2 days of the intervention phase. Researchers will walk the participant through the syncing process and record any reasons for missing data.

At the end of the 30-day period, families will receive a text message instructing them to set up a follow-up call within the next few days. If the participants don’t call within 2-4 days, they will be contacted by the research team. The first follow-up call includes a 10-minute survey for all participants and the questionnaire assessing acceptability and preferences for participants in the intervention arm. After completing the surveys, participants will be asked to choose whether or not to receive text message reminders during the follow-up phase of the study. Automated text messages will be turned on or off for each individual through WTH. All participants will be asked whether they have run out of ICS medication and if they had any problems using the electronic sensor. Any problems that may lead to missing data will be recorded. The participant will then be reminded to transfer the electronic sensor to their new inhaler if or when the prescription is refilled.

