**Methods:**

Participants will include 40 children aged 2-13 years, who are currently admitted to the Children’s Hospital of Philadelphia (CHOP) for asthma, and their parent or legal guardian. Participants will be assigned to intervention and control arms using a 1:1 randomization scheme. The intervention arm will receive daily text message reminders for a 30-day intervention phase following hospitalization. This will be followed by a 30-day follow-up phase, in which all participants may choose whether or not to receive the text messages. Feasibility will be assessed by measuring (1) retention of the participants through the study phases and (2) perceived usefulness, acceptability, and preferences regarding the intervention components. Limited efficacy outcomes will include percent adherence to prescribed ICS regimen measured using Propeller Health sensors and change in parent-reported asthma control. We will perform an exploratory analysis to assess for discrete trajectories of adherence using group-based trajectory modeling (GBTM).

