#### Adherence Trajectories

Finally, we will perform an exploratory analysis to assess for discrete trajectories of adherence using group-based trajectory modeling (GBTM). This analysis will include data from both the intervention and follow-up phases of the study. If no significant differences exist in limited efficacy outcomes between the intervention and control groups, data from both groups will be combined to produce pooled trajectory outcomes.

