#### Follow-up Phase

The follow-up phase begins the day the first follow-up call is completed and continues until 60 days following the start of the randomized intervention. The follow-up phase lasts up to 30 days. Participants will be given 2 weeks following the end of the follow-up period to complete the second follow-up call.

At 60 days, medication adherence monitoring and optional text message reminders will cease and families will receive a message from the study team to set up a second follow-up call (the study completion call) within the next few days. If the participants don’t call within 2-4 days, the research team will contact them. The second follow-up call includes a 10-minute survey for all participants. Participants will be asked again whether they have run out of ICS medication or if they had any problems using the electronic sensor and responses will be recorded. Participants initially assigned to the control group who elected to receive text messages during the follow-up phase will also complete the acceptability and preferences questionnaire.

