#### Trajectories

We will use GBTM to explore daily longitudinal adherence data for different adherence patterns over time. We will specify several models with the best fit using 3, 4, 5, and 6 group solutions, based on quadratic trajectories and a normal probability distribution. We will compare the models to identify the model and number of groups that best fit the data based on the lowest Bayesian information criterion (BIC) and group percentages that are sufficiently large (eg, >5% of the population). These trajectory groups will be used to assess qualitative trends in medication use that may merit further study.

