## Discussion

### Contribution to the Literature

This pilot study will evaluate the feasibility, acceptability, and limited efficacy of a text message reminder intervention to improve ICS adherence in an urban minority population of children with asthma. The study will also assess trajectories of ICS adherence in the 2 months following asthma hospitalization to explore how, when, and why ICS use decays following an acute exacerbation and how this may vary between different families.

While there is a substantial body of literature investigating the reasons for poor adherence to asthma controller medications [3-5], traditional approaches to improving adherence have demonstrated inconsistent results [14-17]. New reminder systems that leverage mobile technology have demonstrated promise in improving adherence in certain populations [18,19,35], but how these technologies and interventions may work in cohorts with the highest levels of asthma morbidity and death has not been thoroughly investigated. This study will add to the literature by providing foundational feasibility data on which components of a mobile health text-message reminder intervention are acceptable and useful and which components may need to be modified to suit the needs and constraints of high risk populations.

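### Second-month trajectory shapes will reflect each family's own choice about reminders as well as post-discharge decay (minor; exploratory analysis)

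*Protocol article*

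**What the plan says.** The protocol article (Intervention Phase) limits the randomised exposure in time: "The randomized intervention begins the day of discharge from the hospital and lasts 30 days". The Abstract (Methods) says that in the next phase "all participants may choose whether or not to receive the text messages". The choice is made at the first follow-up call, where "participants will be asked to choose whether or not to receive text message reminders during the follow-up phase of the study", and it is carried out family by family: "Automated text messages will be turned on or off for each individual through WTH".

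The date of the change is not common to all families. The section on the follow-up phase has it start when a family completes its first call and run to day 60. Families have 2-4 days to call before staff contact them, so the change falls at or some days after day 30. The same section expects some control families to opt in, since it has them complete the acceptability questionnaire.

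On the trajectory model, the Adherence Trajectories section says: "This analysis will include data from both the intervention and follow-up phases of the study". The Trajectories section under Data Analysis specifies solutions with 3 to 6 groups, "based on quadratic trajectories and a normal probability distribution". It states no reminder term, no break at the switch and no split by phase. The Discussion gives the purpose as exploring "how, when, and why ICS use decays following an acute exacerbation and how this may vary between different families".

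**The concern.** The period whose course is to be described is about 60 days long, and roughly halfway through it the exposure can change by the family's own decision. Four reminder histories result: off throughout, off then on, on then off, and on in both months (possibly with a short gap before the call). A curve that is a function of time alone cannot tell a change in reminder status from a change in the family's underlying habit.

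The article's rule on pooling the arms does not guard against this. It depends on the limited efficacy outcomes, which cover the first 30 days: adherence in the intervention phase, and asthma control from enrolment to the 30-day call. A null result there says nothing about second-month switching. Analysing the arms separately does not help either, because each arm can contain both switchers and non-switchers. The Limitations section does not mention the self-chosen switch.

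At stake is the reading of the curves. A family that opts in may look as if its use held up, and one whose reminders stop may look like a steep decliner, although their underlying course is the same. Choice may also track motivation, so second-month contrasts between histories are not randomised contrasts.

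**Working it through.** The article gives no reminder effect, natural decline or opt-in share, so there is no stated figure to reproduce. What follows is an illustration under assumptions.

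**Inputs from the article.** Window of days 1-60; randomised reminders to day 30; self-chosen status from the first follow-up call; quadratic curve in time.

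**Assumed inputs.** Underlying adherence falls linearly from 60% (day 1) to 30% (day 60) in every family: n(t) = 60 − 30(t − 1)/59. Reminders add D = 15 points on days when they are on. The opt-in family switches on at day 35. The family whose reminders stop has them on through day 30. There is no noise.

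**Method.** For each history, fit a + bt + ct² by least squares to n(t) + D × (reminder on at day t), t = 1 to 60.

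| History | Fitted curve | True day 60 | Fitted day 60 |
|---|---|---|---|
| off-off | 60.508 − 0.5085t | 30.0 | 30.0 |
| off-on from day 35 | 58.354 − 0.3900t + 0.00410t² | 45.0 | 49.7 |
| on-off after day 30 | 79.449 − 0.8836t | 30.0 | 26.4 |
| on-on, gap on days 31-34 | 77.295 − 0.7651t + 0.00410t² | 45.0 | 46.1 |

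**Splitting the gap.** Off-on minus on-off at day 60: 49.7 − 26.4 = 23.3 points. The true difference is 45 − 30 = 15, which is the assumed reminder effect. The remainder is misfit: (49.7 − 45.0) + (30.0 − 26.4) = 4.7 + 3.6 = 8.3 points. Neither part is a difference in underlying decay, which is identical by construction.

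**Smearing into the first month.** The underlying change over days 1-30 is −30 × 29/59 = −14.7. The on-off curve shows −0.8836 × 29 = −25.6. The off-on curve goes from 58.0 to 50.3, a change of −7.6 (before rounding the endpoints). Neither family changed status in those 30 days.

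**Second month.** The underlying change over days 31-60 is again −14.7. The off-on curve moves only from 50.2 to 49.7.

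**Sensitivity.**
- Off-on day-60 value: 43.1 for D = 10 and 56.3 for D = 20.
- Off-on turning point, −b/(2c): day 47.6 for D = 15, but about day 79 for D = 10, which is outside the window.
- Flat true adherence, reminders stopped after day 30: the fit shows a false change over days 31-60 of −3.6, −7.3 or −14.5 points for D = 5, 10 or 20. Starting reminders after day 30 gives the mirror image.
- D = 0, or no change of status: no distortion.

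**The case against.** The strongest reply is that the analysis is labelled exploratory, is meant to show qualitative trends for further study, and comes from a trial that says it is not powered for trajectories. The article never claims that the curves show natural decline. The optional phase has its own use, since uptake after day 30 bears on acceptability. A detailed model specification may also sit in a fuller document that is not shown. All of this stands, and it keeps the point minor. It does not dispose of it: low power concerns random error, whereas this mixing is systematic and more families would not remove it. The article itself fixes both the data window and the curve form that produce it.

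A second reply is that extra latent groups might absorb the switchers. They might, in part, but those groups would then partly describe reminder choice.

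A reader might infer more than the documents support:
- *The whole day-60 gap is artefact.* It is not. Under the illustration, 15 of the 23 points are a real difference in medication use, which a trajectory model ought to show.
- *The decline disappears or reverses.* That depends on the assumed effect. At 15 points the flattening is confined to the second month, and the off-on curve still falls from 58.0 on day 1 to 49.7 on day 60. At 10 points it falls throughout the window.
- *The trajectory groups will simply be the reminder histories.* Nothing in the article establishes this, as the effect and the opt-in share are unknown.
- *A reminder covariate would yield curves free of reminder status.* It would not, because status is self-selected.

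**Conclusion.** The point holds as a minor one about interpretation. As written, the plan combines self-chosen reminder changes with post-discharge decay in one quadratic per trajectory group, and no stated safeguard separates them. Under the assumed 15-point effect and common decline, curve misfit adds about 8 points to a real 15-point difference at day 60, and first-month slopes are distorted as well. The size scales with the reminder effect and with the number of families who change status, neither of which the article gives; with no effect or no switching this distortion is nil. It would be wrong to infer that the trial's main results are compromised: the randomised 30-day adherence comparison and the primary feasibility outcomes do not use the second-month curves.

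**What to change.** 1. Extract each family's reminder on and off dates from the messaging platform, where status is already set individually. Define a category for families who never complete the first follow-up call.
2. Show adherence on days 31-60, and trajectory-group membership, by reminder history, and label both as non-randomised.
3. Base statements about decay without reminders mainly on control-arm days 1-30. Show reminder-off follow-up days beside them as self-selected.
4. Optionally, add a time-varying reminder term as a sensitivity analysis. With 40 children and a group-size threshold of about 5% (40 × 0.05 = 2), a group just above it could hold three children, and a group-specific term may be inestimable there. Use a term common to all groups if necessary, and do not claim that it removes self-selection.
5. Add a sentence to the Limitations on the self-chosen switch.

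The work is small, as the platform should already hold the dates. The real cost is a narrower claim about the second month: the control-arm days 1-30 rest on about 20 children and cover only half of the two-month aim. Trial conduct does not change.
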